#### fMRI Examination

Resting-state fMRI data processing and analysis will be conducted using DPABI (Chao-Gan Yan) and SPM12 (Functional Imaging Laboratory) software with the MATLAB platform.

##### Preprocessing

The initial 10 time points will be removed, and corrections will be made for both time and head movements. Data with head movements exceeding translations of >2 mm or rotational shifts of >2° will be excluded. Linear drift will be removed, and regression will be applied to remove interference from white matter, cerebrospinal fluid, and the whole brain signal. Functional images will be registered to T1 gray matter structural images, followed by spatial smoothing with a Gaussian kernel (4-mm half-width height), delinearization, drift correction, and filtering within the range of 0.01-0.1 Hz. All data from participants will be assessed for quality.

##### Methods for Brain Functional Network Connectivity Analysis

The amplitude of low-frequency fluctuation (ALFF) method will be employed to calculate changes in brain-wide low-frequency amplitudes before and after treatment. Brain regions identified in the ALFF results, related to the study hypothesis, will serve as seed points. The average time series of these seed regions and their domain signals will be extracted, and correlations with the remainder of the whole brain will be calculated.

### Ethical Considerations

The study protocol complies with the ethical standards of the Declaration of Helsinki. The Ethics Committee of Guang’anmen Hospital has approved the study protocol (approval number: 2022-114-KY; September 7, 2022), which has been registered in the Chinese Clinical Trial Registry (trial registration number: ChiCTR2200066274; registered on November 30, 2022). The investigators have the responsibility to fully and comprehensively introduce the purpose, procedures, possible risks, and subsidy of this study to the participants and get signatures on 2 informed consent forms, one kept by the participant and the other kept by the researcher, which should be retained as a clinical research document for reference. The participants will receive a subsidy of 300 CNY (US $41.27) through bank transfer after completing treatment and follow-up. All participants will be free to participate in this study and can decide to withdraw at any time. During the study process, the privacy and confidentiality of the participants will be protected. Each participant’s name will be replaced by a serial number and initials. Their personal information will not be disclosed when the paper is published, and the results will be published regardless of whether the research is positive or negative.

## Results

Recruitment began on March 1, 2023. A total of 4-6 participants are expected to be enrolled per month. The recruitment is planned to be completed on March 1, 2025, and we expect to publish our results by the winter of 2025. As of November 1, 2023, we have enrolled 25 participants with CSU.

To compare all the results, including both primary and secondary outcomes, and evaluate the treatment effect, we will use R (version 4.0.1) for the analyses. ANOVA and independent samples *t* tests will be repeatedly performed for determining differences in variables between baseline and posttest in the treatment and control groups and for comparing the effects of the program between the groups. Moreover, we will determine whether there is a significant difference between the groups by judging the rejection range based on a significance level of .05. Drawing upon the outcomes of prior research, we anticipate that when comparing the primary and secondary efficacy indicators across the intervention and baseline periods, both the treatment and control groups will exhibit a downward trend in scores. However, it is expected that the decrease will be more pronounced and significant in the treatment group.

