**Methods:**

This is a randomized, double-blind, placebo-controlled trial. In this trial, 108 participants aged 18-60 years with a diagnosis of CSU and no history of ACE will be randomly assigned to 2 groups (1:1 ratio) using the Statistical Analysis System: treatment (ACE) and control (sham ACE). The participants and efficacy evaluators will be blinded to the grouping. Both the ACE and sham ACE groups will undergo acupuncture, but the sham ACE group will not receive catgut sutures. Treatment will be performed twice weekly for 8 weeks, with a 1-week run-in period and a 16-week follow-up period. Twenty patients will be randomly selected to undergo functional magnetic resonance imaging before and after the treatment period. The primary outcome will be the urticaria activity score over 7 days (UAS7). We will use R (version 4.0.1; R Project for Statistical Computing) to perform ANOVA and independent samples *t* tests to compare the differences within and between groups before and after treatment by judging the rejection range based on a significance level of .05.

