### Outcomes

The study schedule is presented in Figure 3. All outcome measures explained below will be recorded from baseline until the end of follow-up.

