#### Primary Outcome

The primary outcome measure for this clinical trial will be the UAS7. The UAS7 is the gold standard for CSU, evaluating 2 skin symptoms: wheals and itching. Participants will self-assess and record the severity of their symptoms on a 4-point scale. For itchiness, the scoring will be as follows: 0, no symptoms; 1, mild symptoms (occasional itching, no scratching, and no effect on life and sleep); 2, moderate symptoms (occasional itching, scratching, and life and sleep slightly disturbed, but tolerable); 3, severe symptoms (frequent itching, scratching, life and sleep disturbed, and intolerable). For wheals, the scoring will be as follows: 0, no symptoms; 1, mild symptoms (<20 in 24 h); 2, moderate symptoms (21-50 in 24 h); 3, severe symptoms (>50 in 24 h or large confluent masses). The UAS7 ranges from 0 to 42, with lower scores indicating milder skin symptoms [23].

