### Oversight and Monitoring

#### Data Collection and Management

The investigator will prepare original documents for each participant upon their random entry into the study. All pertinent information will be documented in the CRFs weekly and saved in a Microsoft Excel spreadsheet. The fMRI results will be archived on a CD-ROM. To ensure data integrity and quality, an internal data supervision team of researchers, led by the principal investigator, will oversee and audit clinical data. They will regularly or sporadically review the CRFs and promptly provide feedback to researchers in case of any identified issues to prevent the recurrence of similar errors or omissions. It is important to note that all participant data will be strictly confidential and not accessible to the public.

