### Statistical Methods

#### Primary and Secondary Outcomes

Continuous variable data following a normal distribution will be expressed using means (SDs), while those not following a normal distribution will be expressed using medians and quartiles. Categorical data will be depicted as component ratios or percentages. Group comparisons for continuous variables will be conducted using independent samples *t* tests and repeated-measures ANOVA (multiple time-point comparisons). Nonparametric data comparisons will be carried out using rank-sum tests. Categorical variables will be compared using chi-square tests or Fisher exact tests. All data analyses and graph representations will be processed using R 4.0.l software (R Project for Statistical Computing). Statistical significance will be defined as *P*<.05.

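### The UAS7 comparison that decides the trial is not fixed, and several unranked tests at .05 do not hold its error at 5%

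*Protocol article*

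**What the plan says.** - **Outcome.** Primary Outcome section: "The primary outcome measure for this clinical trial will be the UAS7". The section describes the scoring but attaches no week and no contrast (value at a visit, change from baseline, or average over visits).
- **Span.** Outcomes section: "All outcome measures explained below will be recorded from baseline until the end of follow-up". By the Study Design section this covers 8 weeks of intervention and 16 weeks of follow-up.
- **Tests.** Statistical Methods, Primary and Secondary Outcomes: continuous variables are compared between groups by "independent samples *t* tests and repeated-measures ANOVA (multiple time-point comparisons"), with significance at P<.05.
- **Tests again.** The Abstract says ANOVA and t tests will "compare the differences within and between groups before and after treatment by judging the rejection range based on a significance level of .05". The Results section says that ANOVA and t "tests will be repeatedly performed for determining differences in variables between baseline and posttest in the treatment and control groups" as well as between groups, and that "we will determine whether there is a significant difference between the groups by judging the rejection range based on a significance level of .05".
- **Sample size.** One two-group comparison of UAS7, about 40 per group, 54 after 25% dropout. No time point is tied to it.

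**The concern.** The article describes its analysis in three places (Abstract, Statistical Methods, Results). None says which UAS7 result answers the primary question. A t test and a repeated-measures ANOVA are both available, more than one time point is in play, and .05 applies to each.

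The choice is a live one, because the rationale supports more than one time point. The before-and-after wording points to the end of treatment. The ACE Approach section says catgut is withheld from controls to see whether ACE extends the duration of effect, which points to follow-up. The Discussion claims both a fast onset and a prolonged effect.

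The trial aims at definitive evidence. If the deciding comparison is chosen once results are known, the primary P value has no known error rate, and no later analysis can restore it.

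**Working it through.** **1. The plan's own figure.** The formula itself is missing from the text. I read 9.12 as the SD and 6 as the difference, because this reproduces the stated n. With the article's 1.64 and 1.28:

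n = 2 × (1.64 + 1.28)² × (9.12/6)² = 2 × 8.5264 × 2.3104 = 39.4, so about 40 per group. Dropout: 40/0.75 = 53.3, so 54.

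Both stated figures are reproduced. They rest on a single test at one-sided .05 with 90% power.

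**2. Narrow reading: baseline and one posttest.** Simulation with 40 per group, no true difference, two-sided tests at .05 and 20,000 replicates. With two occasions, the ANOVA group-by-time test equals a t test on change, and the ANOVA group effect equals a t test on the mean of the two occasions.

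| Baseline-posttest correlation (assumed) | Posttest t test only | t test or group-by-time | Also allowing group effect |
|---|---|---|---|
| 0.3 | 5.0% | 8.9% | 11.5% |
| 0.5 | 5.0% | 9.1% | 11.3% |
| 0.7 | 4.8% | 9.3% | 11.1% |

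**3. Several time points.** Chance of at least one significant between-group t test among k, with no true difference, 40 per group, two-sided .05 and 8,000 replicates. Both k and the correlation are assumptions. The independent case is 1 − 0.95^k.

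| k | Independent | Exchangeable 0.5 / 0.7 / 0.8 | AR(1) 0.5 / 0.7 / 0.8 |
|---|---|---|---|
| 1 | 5.0% | 4.3 / 5.0 / 5.2% | 5.0 / 5.1 / 5.3% |
| 2 | 9.8% | 9.0 / 8.6 / 8.1% | 8.8 / 8.3 / 8.3% |
| 4 | 18.5% | 16.6 / 13.2 / 11.2% | 16.2 / 14.2 / 12.8% |
| 8 | 33.7% | 25.0 / 19.6 / 15.3% | 29.1 / 25.3 / 21.2% |

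At a correlation of 0.9 the rates fall to 9-10% for k = 4 and 12-16% for k = 8.

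**4. What is not counted.** Within-group tests of baseline against posttest do not test the treatment effect. The Results section itself expects both groups to fall, so a significant within-group change is not a false-positive primary result.

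**The case against.** - **The Results sentence names only baseline and posttest.** Its wording about repetition may be a garbled form of repeated-measures ANOVA, or may mean repeated for each variable. This stands: support for several time points comes from the Statistical Methods and Outcomes sections.
- **No rule says that any significant time point wins.** A reader might infer such a rule from repeated tests at .05, but no section states it. The inflation is conditional on how the results are read.
- **Recording is not testing.** The Data Collection and Management section says "All pertinent information will be documented in the CRFs weekly". A reader might infer a test of UAS7 at each of the 8 + 16 = 24 weeks, but no section plans that, so no error rate should be quoted for it.
- **One repeated-measures ANOVA is one model.** Its group-by-time test, taken alone, can be held at 5%. This is true, but the article lists the t test beside it without saying which decides.
- **The wording leans towards end of treatment.** This is also true, and it guides the fix. It still does not choose between t test and ANOVA or name a week.
- **Ranking of tests and multiplicity are often left to an analysis plan or full protocol, not shown here.** This stands for the secondary outcomes. The primary time point and contrast belong in the protocol itself. The missing schedule figure would show when visits occur; its caption does not suggest that it marks one as primary.

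**Conclusion.** The point holds as an unfixed primary comparison with several unranked tests, each at .05. If one test decides, the error is 5%. If any significant between-group result may be presented as primary, it is about 9% with a single posttest, 11-17% with 4 time points and 15-29% with 8.

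These figures assume two-sided tests, 40 per group and, for several visits, a between-visit correlation of 0.5 to 0.8. The number of visits is not in the text. The excess over 5% may therefore be moderate or large, and the documents do not settle which.

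**What to change.** Before unblinding, amend the protocol and registry entry to name:

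1. One between-group UAS7 comparison at one time point. End of treatment (week 8) best fits the before-and-after and baseline-to-posttest wording. If the sponsor regards duration of effect as the main question, a follow-up time point may be named, but only one.
2. One test: either the t test or a specified ANOVA term.
3. Its sidedness. The sample size uses one-sided .05. If the test is two-sided, 40 per group gives 6/(9.12 × √(2/40)) = 2.94, and 2.94 − 1.96 = 0.98, so about 84% power instead of 90%. Two-sided 90% would need 49 per group before dropout.
4. The status of everything else. Other time points, including the 16-week follow-up, and the within-group tests are secondary or supportive. Reword the Results sentence on repeated testing to match.

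The cost is wording only. No new data are needed, and the planned N already assumes a single comparison, so naming one does not change it. The Randomization section puts unblinding at the end of case collection, and the Amendments section provides the route. The downside is that fewer time points can carry a claim of significance. If the full protocol or analysis plan already names the comparison, only the public wording needs aligning.

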## Discussion

We hypothesize that wheals and itching will show greater improvement in participants receiving active therapy than in those receiving sham treatment. The results of this study will provide new insights into the effects and mechanisms of acupoint stimulation in the treatment of CSU, aiming to reduce the disease burden and economic cost and to contribute to both academia and public health.

ACE, a variant of acupuncture therapy, is based on the theory of acupuncture in TCM and employs absorbable surgical sutures to produce long-lasting acupoint stimulation in the human body [27]. While the specific mechanism of action remains under investigation, it is believed to be associated with improved local circulation, inhibition of the release of inflammatory factors, reduction in apoptosis, and regulation of cellular factors [28]. Currently, ACE is not widely used to treat skin diseases. However, research and evidence-based medicine [29] have demonstrated that ACE is more effective compared to acupuncture and medicine for the treatment of chronic diseases related to the immune system, such as psoriasis [30], allergic rhinitis [31], and ulcerative colitis [32]. Referring to some research studies [33-35] and previous experience, we designed a randomized, double-blind, placebo-controlled trial to observe the therapeutic effect of ACE on CSU by comparing the outcomes before and after treatment. To the best of our knowledge, this is the first study to use ACE for CSU and to observe its clinical efficacy.

This study will employ ACE—an evolved form of acupuncture—as the primary intervention owing to its swift onset, prolonged effects, and improved compliance. We will enroll 108 CSU patients and conduct a randomized, double-blind, sham-controlled study to corroborate the therapeutic benefits of ACE. Additionally, we will use fMRI to delve into the central mechanism of this therapy and validate the hypothesis of modulating the “cerebellum-limbic lobe-reward-somatosensory circuit,” thereby providing robust clinical evidence for the acupuncture treatment of CSU. Compared with previous studies, this study has a larger sample size, less frequency of treatment, and a higher patient compliance rate.

However, this study has certain limitations. On the one hand, this trial is a single-site randomized controlled trial involving a relatively limited number of CSU patients. In our subsequent phase, we aim to embark on a multicenter clinical study to expand the participant pool and thereby enhance the generalizability of our findings. On the other hand, this study requires the enrollment of patients aged 18-60 years with a UAS7 of ≥16. However, this selection criterion may exclude some patients with mild symptoms, patients who can effectively control their condition with medication, and younger or older patients, thereby preventing them from receiving ACE treatment. Furthermore, this study only involves an 8-week intervention for patients, and there may be patients who require a longer period of treatment to achieve significant effects.

If ACE is proven to be effective, it could lead to comparisons with acupuncture or pharmaceutical treatments, offering evidence to support ACE as a novel nonpharmacological approach for CSU management. Furthermore, we can endeavor to integrate modern and traditional techniques to develop a medicinal thread as a potential material for ACE. After the research results are released, we will promote the acupuncture treatment plan for CSU through academic conferences, training courses, standardized training, and other forms of promotion. Moreover, we will promote this project at corresponding community health service centers and support institutions. Through academic exchange, guidance, and article publication, we will promote the academic achievements of this project nationwide, which will facilitate the transformation, promotion, and application of the research results.

## Abbreviations

ACE: acupoint catgut embedding
ALFF: amplitude of low-frequency fluctuation
BOLD: blood oxygenation level–dependent
CRF: Case Report Form
CSU: chronic spontaneous urticaria
CU-Q2oL: Chronic Urticaria Quality of Life Questionnaire
DLQI: Dermatology Life Quality Index
FA: flip angle
fMRI: functional magnetic resonance imaging
FOV: field of view
HPA: hypothalamic-pituitary-adrenal
MRI: magnetic resonance imaging
TCM: traditional Chinese medicine
TE: time to echo
TR: time to repetition
UAS7: urticaria activity score over 7 days
